### Setting

This study is conducted through two health-care systems, University of California, San Diego (UCSD) and Scripps, with a total of five hospitals. These hospitals have a combined licensed capacity of over 1,400 beds (Scripps has 873 and UCSD has 531) and are responsible for over 65,000 inpatient admissions each year. Estimates for smoking prevalence among these inpatients are 15 to 20%, providing a large pool from which to recruit. San Diego has a diverse population, including a large Latino population, which is reflected in the hospital population. Quitline counseling is provided by the California Smokers’ Helpline (CSH), the state quitline that is centrally operated from San Diego.

### Study population

Subjects will be 1,640 English- and Spanish-speaking adult smokers (18 years and over) hospitalized at one of the participating hospitals.

#### Eligibility criteria

Hospitalized smokers are eligible for inclusion if they are adults who smoked in the previous 30 days and are interested in staying quit (or planning to quit) upon discharge. Subjects must speak English or Spanish and provide sufficient contact information for intervention and evaluation (for example, name, address, phone number). They must provide signed informed consent and must receive physician approval for study participation.

Exclusion criteria include an anticipated hospital stay of less than twenty-four hours (shorter stays do not provide sufficient time for the assessment, consent, and intervention), inability to communicate or provide signed informed consent, or smoking fewer than six cigarettes per day. Pregnant smokers are not included in this study because there is still debate about the advisability of using nicotine patches during pregnancy [19,20].

### Sample size

This study uses a factorial design and was powered by marginal means (that is, the mean of the counseling factor averaged across levels of the nicotine patch factor) rather than the interaction. Sample size estimates were conducted using R [21]. Based on pilot work conducted in one of the hospitals with 120 patients, we assume the abstinence rates at six months will be 7% in usual care, 14% in proactive quitline counseling, 14% in the group receiving patches at discharge, and 21% in the group receiving both proactive counseling and patches [17]. Simulating binomial data from the assumed distribution, fitting generalized linear (binomial) models to the resulting data, and applying Hochberg’s (1988) [22] set-up procedure to the results, indicates that 298 subjects per cell is sufficient to have 80% power to see both main effects with the family-wise error rate controlled at the 0.05 level (two-sided). Assuming a variance inflation of 10% due to clustering and average follow-up rates of 80%, we need 410 subjects per cell - or 1,640 total - to have the same power for the mixed-effects complete-case analysis of the primary outcome with composite Type 1 error rate ≤ 0.05 (two-sided).

Hospital records suggest that about 30% of admitted smokers have cardiovascular or pulmonary diseases. This means, about 492 of the 1,640 subjects will be in this group, which allows for analysis of the moderating effects of diagnosis on interventions.

### Human subjects’ approval

This study is funded by the National Cancer Institute through a U01 mechanism. It has received ethics approval from the University of California San Diego Human Research Protection Program (HRPP) (Number 110410), the Scripps Hospital System Internal Review Board (IRB) (Number 11-5695) and the Consortium of Hospitals to Advance Research on Tobacco (CHART) Data and Safety Monitoring Board (DSMB). Information about study subjects is kept confidential and managed according to the requirements of the Health Insurance Portability and Accountability Act (HIPAA) [23].

### Procedures

#### Recruitment process

This study is an effectiveness trial; therefore, every effort is made to embed the recruitment process into the current work flow of the hospital (Figure 1). The health-care systems have different procedures for addressing smoking with their patients. As a result, there are two recruitment/implementation models that differ in who has the responsibility for each task and in the degree to which they rely on automated processes through the electronic medical record (EMR). Both hospital systems routinely assess smoking status of all patients at the time of admission and record this information in the electronic medical record. As part of routine care, each day a list of recently admitted smokers is generated and designated hospital staff visit the smoker at bedside to provide a brief cessation intervention. In this study, the bedside visit is used to assess the patients’ eligibility for the study and to obtain signed informed consent. Patients who are not eligible for the study or not interested in participating receive the current standard of care, which is to provide the toll-free number for the California Smokers’ Helpline ([name]).

**Figure 1 F1:**
[figure not shown]
**Flow diagram of the CHART Trial at UCSD and Scripps Hospitals.** Eligible patients are stratified by hospital and cigarettes per day and randomized into one of four groups in a 2 x 2 factorial design.

In the Scripps hospitals, respiratory therapists (RT) are responsible for recruitment of subjects and for nicotine patch delivery at discharge. They are also responsible for contacting the physician to obtain approval for study participation. Although the medical record is flagged for patients who are randomly assigned to receive nicotine patches, the electronic medical record system is not used for communication between the RT and the physician or pharmacy.

At the UCSD hospitals, subjects are recruited into the study by research staff (aka research recruiter or RR) provided by the CSH research team. The electronic medical record (EMR) is used extensively to communicate between research and hospital staff with many of the processes automated. A daily list of recently admitted smokers is generated from the EMR and is viewable by RRs. The physician approval process is also embedded in the EMR system. In this hospital system, smokers are approved for participation in the study unless physicians indicate in the EMR that they should not participate.

#### Randomization

For this study, the CSH research team established and hosts a secure website that is used to randomize subjects into condition. The website complies with all HIPAA security guidelines for electronic protected health information (EPHI) [24]. All communication between hospitals and the California Smokers’ Helpline (CSH) is encrypted; identifying fields that are stored locally remain encrypted to ensure subject confidentiality. Staff responsible for recruitment and randomization enter the website through a password-protected web portal.

Recruitment staff (that is, RT and RR) complete the eligibility assessment and baseline measures, obtain signed informed consent from the smoker and approval from the physician. To complete the randomization procedure, staff use a web portal developed in-house to access the secure proprietary website. They enter the name, address, medical record number, phone number, cigarettes per day, and the anticipated discharge date of the smoker. The computer checks the name against a list of previously randomized subjects. If smokers are already in the study, a pop-up indicates their treatment condition and prevents re-randomization. If the smoker is not already in the study, the RT or RR confirms that the smoker is eligible, has provided signed informed consent, and that the physician has provided approval for study participation. The computer then randomly assigns the subject to condition. The condition is displayed to the RT or RR and all information is transmitted to CSH daily.

### Interventions

#### Telephone counseling

Telephone counseling is provided by the CSH, a state-funded service that is operated through the Moores Cancer Center at the University of California, San Diego. The quitline, which has been in operation since 1992, provides free cessation services to about 30,000 state residents each year from one location in San Diego, California.

The telephone counseling provided is, in effect, the standard service provided to any smoker who calls the state quitline for help except that a counselor initiates the first call. The telephone counseling uses a combination of social learning theory, cognitive-behavioral therapy and motivational interviewing to increase self-efficacy, resolve ambivalence, encourage new behaviors while changing self-defeating thoughts, and create a solid relapse prevention plan [25-27]. Subject information is uploaded into the CSH database daily and a list is generated each day of clients who need to be called. Counselors make at least 10 attempts to reach the client for the first counseling call. The initial counseling call is a 30 to 40 minute comprehensive session to discuss the client’s quitting experience during and after the hospital stay and to set up or solidify the quitting plan accordingly. After this call, counselors initiate up to eight follow-up calls to assess the client's progress and, as appropriate, discuss and normalize withdrawal symptoms, review proper use of pharmacotherapy, examine slip or relapse situations, revise the plan as needed and bolster self-efficacy and motivation. Follow-up sessions last about 10 to 15 minutes depending on the needs of the client.

The standard quitline telephone counseling has been described in great detail elsewhere [25] but, briefly, it has several distinguishing features including proactive counseling, a structured counseling protocol, and relapse-sensitive scheduling. The content of the counseling addresses both behavioral and cognitive issues the individual smoker faces in an attempt to quit. Calls are front-loaded when the probability of relapse is highest and spaced out as the client experiences success in quitting; such relapse-sensitive scheduling of calls has been shown effective in preventing relapse [28]. The telephone counseling is provided by a program with a mature infrastructure and rigorous quality assurance measures, which facilitates its implementation.

#### Nicotine patches

Providing nicotine patches can help with nicotine dependence. Perhaps more importantly, smokers who put on a nicotine patch at the time of discharge are making a statement of their intention to stay quit after leaving the hospital. Subjects randomized into the patch condition receive an eight-week supply of nicotine patches. At the Scripps hospitals, following randomization, the RT flags the medical record of subjects in the patch conditions and faxes a prescription to the pharmacy. At discharge, the RT retrieves the package of nicotine patches from the pharmacy and delivers it to the subject. At the UCSD hospitals, research staff query the list of subjects randomly assigned to receive patches and contact the pharmacy to prepare the package. Pharmacy staff deliver the nicotine patches to the subject at the time of discharge.

Patches are dosed according to how many cigarettes the subject smoked each day using a step-down regimen. Those who smoked six to ten cigarettes per day receive six weeks of 14 mg (Step 2) and two weeks of 7 mg (Step 3) patches. Those who smoked eleven or more cigarettes per day receive four weeks of 21 mg (Step 1), two weeks of 14 mg (Step 2), and two weeks of 7 mg (Step 3) patches. Subjects in the patch conditions who are not already wearing a patch are told to put on a patch before leaving the hospital.

#### Usual care

All subjects receive the hospital’s standard care (that is, usual care). This care typically includes a brief bedside intervention (<10 minutes) in which an RT or nurse encourages quitting and provides educational materials and the number for the state quitline. If it is not possible to make contact because the patient is sleeping or involved in a test or procedure, staff may leave the materials. Subjects might be provided with nicotine patches during their hospital stay, but this is not typical. There is no systematic assessment of their need for a quitting aid. Such decisions are made by the physician on a case by case basis.

### Data collection and measurements

It is important to gather data for the study in ways that are not overly burdensome for subjects or hospital staff. Therefore, we established some guiding principles for data collection. First, if data are already part of the electronic medical record, the information is obtained directly, rather than asking the subject to provide it again. This not only reduces the time for staff and subjects, it minimizes errors. Second, only essential items are collected at baseline. These items include those that: are needed to ensure eligibility for the study, allow delivery of the appropriate intervention, or are measures CHART has determined to be ‘core measures’ [29]. Third, sufficient data are collected at two- and six-month evaluations to allow analysis of multiple outcomes such as thirty-day abstinence, quit attempt rate, and prolonged abstinence. Fourth, process data regarding the counseling and patch intervention are collected throughout the study.

#### Data collection points

Initial data are collected from subjects while they are in the hospital (baseline). Subsequently there are evaluation calls at two and six months after baseline.

#### Measurements

All data that are considered ‘core measures’ to the CHART trials are collected [29], as well as additional data relevant to the interventions. The trial will be reported using the CONSORT guidelines for transparent reporting of trials [30].

### Baseline measures

Contact information (for example, name, address and phone), hospital site, medical record number, admission date and time, demographics (for example, age, sex, ethnicity/race, education, marital status, and type of insurance), and height and weight (used to determine BMI) are obtained from the medical record [29]. Other information that is required to assess eligibility and to measure the baseline is obtained directly from the subject. Subjects’ smoking status (that is, smoker versus nonsmoker) is based on the criterion of whether they report having smoked in the last 30 days. Other tobacco variables obtained at baseline include the number of days the subject smoked in the last 30, number of cigarettes smoked per day on average, use of any other form of tobacco, history of smoking since being admitted to the hospital, and confidence to stay quit after discharge. Subjects are only eligible for the study if they intend to stay quit (or plan to quit) after discharge. Because one intervention is the nicotine patch, subjects are asked about possible contraindications for nicotine patch use (that is, high blood pressure, heart attack, stroke, arrhythmia, angina and a history of severe allergic reaction to adhesive tape). Subjects who have a possible contraindication to using the nicotine patch are still eligible for the study, provided the physician approves.

### Discharge information

As part of the CHART consortium, this project gathers core measures about discharge from the medical record [29]. These measures include: discharge plan (home, skilled nursing facility, or other placement), discharge date and time (used to determine length of hospital stay and report timing of intervention activities), and information regarding diagnosis (that is, primary and secondary discharge diagnosis, diagnosis-related groups (DRG), and procedure codes).

### Evaluation measures

At two and six months, subjects are called by the UCSD evaluation team, a group that is independent of the quitline counseling staff. Up to 30 attempts are made to reach subjects before being coded as a ‘no contact’. Two weeks prior to the evaluation, a letter is sent to remind subjects of the research and to encourage their participation in the evaluation. Each letter includes a non-contingent incentive (a $2 bill), which has been shown to increase participation rates [31]. Subjects receive $20 to complete each evaluation. Evaluation includes a series of questions about satisfaction with services received, current smoking status, and the history of quitting since enrolling in the study. Evaluators also ask about confidence in quitting or staying quit, presence of other smokers in the home, and use of other behavioral counseling services or quitting aids (nicotine patches or other nicotine replacement therapy, Zyban or Chantix).

Our study is participating in the CHART biochemical verification study as described in Riley *et al.*, which aims to obtain an estimate of the validity of self-report across consortium projects [28]. Subjects who indicate they are not smoking at the six-month evaluation are offered $100 to return a saliva sample, which is then tested for cotinine levels at Salimetrics laboratory in Pennsylvania [32]. In addition to providing data from these subjects to the consortium’s verification study, we have embedded a randomized design into the cotinine procedure that will test the impact of the amount of incentive offered and the smoking status on the rate of compliance with the saliva sample request. Stratifying by smoking status at the six-month evaluation, all self-reported nonsmokers and a random selection (25%) of self-reported smokers will be randomly assigned to be offered $20 or $100 for the return of the saliva sample. The results from the self-reported nonsmokers who were offered $100 will be included in the CHART biochemical verification study. The remaining conditions will allow us to determine whether smoking status and size of the incentive offered affect the return rates, information that can inform subsequent work in the area of hospitalized smokers.

At the two- and six-month evaluations, subjects are asked about whether they have been re-admitted to a hospital since their enrollment in the study. Information is obtained about length of each stay and reason for admission. In addition, research staff will perform a chart review of hospital records for enrolled subjects to determine re-hospitalization rates. If the chart review indicates relatively high accuracy of self-report, analysis of re-admission will use self-report data.

### Process measures

Every opportunity is taken to collect data about the implementation and fidelity of the various interventions. The number of smokers assessed and provided with brief counseling is obtained from hospital records. We track whether nicotine patches were distributed as planned or whether the patches were sent after discharge. The number and timing of proactive calls made to engage subjects in counseling is tracked in the quitline database. Other information tracked includes subjects’ participation in quitline counseling and the number of counseling calls provided. The quitline also routinely tracks the content of the counseling calls, and the length and timing of calls relative to the quit date, a process that is monitored for this study as well.

### Analytic plan

#### Primary aims

The primary aim of this study is to determine the effect of proactive telephone counseling and nicotine patch use on successful quitting among hospitalized smokers. The unit of analysis is the individual, but we anticipate some clustering due to commonalities in subjects admitted to individual hospitals (and, correspondingly, variability between hospital populations). generalized linear (binomial) mixed models are used to study the effect of treatment and clustering is accounted for with hospital-specific random effects [33]. The primary outcome is self-reported thirty-day abstinence at six months. The primary analysis is intent-to-treat and focuses on assessment of the main effects associated with proactive quitline counseling and receipt of nicotine patches at discharge. Analyses will be performed using SAS software (version 9.2, SAS Institute, Cary, NC). Although the study was not powered to detect an interaction, the interaction between the two treatments is assessed as a secondary outcome, as is seven-day abstinence, and the disagreement between cotinine-validated abstinence and seven-day self-reported abstinence. We will use Hochberg’s [22] step-up procedure to ensure a family-wise error rate/composite Type I error of ≤0.05.

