## Methods

### Design

This study uses a 2 x 2 (patch by counseling) factorial design. Hospitalized patients are recruited from two health-care systems in San Diego County. Subjects provide signed informed consent and are randomly assigned by the computer to one of four conditions: usual care, proactive quitline counseling, nicotine patches at discharge, or both, in a 2 x 2 factorial design with an equal number of subjects per cell. Randomization is stratified by hospital and cigarettes per day (six to ten or eleven plus) and uses blocks of eight to keep a balance of characteristics across the four conditions. Smoking status is evaluated at baseline, two and six months after discharge. Cotinine-validated smoking status is assessed on all subjects who report abstinence and a random sample (25%) of subjects who report continued smoking at six months.

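### Cigarettes per day is one of the two randomisation strata but has no stated role in the primary model; adding it as a prespecified covariate is a small, free improvement

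*Protocol article*

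**What the plan says.** The Design section of the protocol article states: "Randomization is stratified by hospital and cigarettes per day (six to ten or eleven plus) and uses blocks of eight". The Setting section describes two health-care systems "with a total of five hospitals". If each hospital is its own stratum, there are 5 x 2 = 10 strata.

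Under Primary aims in the Analytic plan, the outcome is binary: "The primary outcome is self-reported thirty-day abstinence at six months". The analysis "focuses on assessment of the main effects associated with proactive quitline counseling and receipt of nicotine patches at discharge", using a generalized linear (binomial) mixed model in which "clustering is accounted for with hospital-specific random effects". The abstract gives the same model. The Sample size section calls it a mixed-effects complete-case analysis.

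These places name two kinds of term: the treatment effects and the hospital effect. None of them mentions cigarettes per day. The Nicotine patches section uses the same cut-off of 6 to 10 versus 11 or more to set the patch regimen.

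**The concern.** An analysis normally reflects the factors by which allocation was restricted. The article says how one stratification factor enters the model and gives the other no role. A statistician who followed the Primary aims text to the letter would fit treatment plus hospital and stop there.

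Three things could be at stake if cigarettes per day predicts abstinence:

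- The treatment odds ratio from a model without it sits slightly closer to 1 than the odds ratio conditional on it.
- Model-based standard errors ignore the balance that stratification created, so tests become slightly conservative and a little power is lost.
- Balance at randomisation need not survive among completers. The article plans for 80% follow-up. If loss depends on arm and smoking level together, a model without the stratum can show a treatment difference that is only a difference in case mix.

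A covariate left unfixed can also be added, or not, after the data are seen.

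**Working it through.** **1. The plan's own figures.** The inputs, from the Sample size section, are abstinence of "7% in usual care, 14% in proactive quitline counseling, 14% in the group receiving patches at discharge, and 21"% with both interventions, 298 per cell, and "Assuming a variance inflation of 10% due to clustering and average follow-up rates of 80"%.

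- Inflation: 298 x 1.10 / 0.80 = 409.75, so 410 per cell, and 4 x 410 = 1,640. This matches exactly.
- Margins for each factor: (7 + 14)/2 = 10.5% and (14 + 21)/2 = 17.5%.
- Base size: testing each effect at 0.025 with power sqrt(0.80) = 0.894 needs 598 per margin, or 299 per cell. At 596 per margin the joint power is 0.894 squared = 0.799. So 298 is reproduced on that reading.
- With Hochberg's rule taken literally (both effects declared when both p-values are at most 0.05), simulation of the main-effects logistic model gives 88% joint power at 298 per cell. The stated size is therefore not too small.

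**2. Assumptions for the comparison.** The article does not say how many subjects smoke 11 or more per day, how strongly this predicts abstinence, or how much hospitals differ. I assumed 60% in the 11+ stratum, a stratum odds ratio for abstinence of 0.7, 0.5 or 0.35, five unequal hospitals with a logit standard deviation of 0.3, and 6,000 simulated trials per scenario. Hospital is in both models, as a fixed effect for speed, so the only difference is the cigarettes-per-day term. The null scenarios use 14% abstinence in all four cells.

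**3. Power and type I error, without -> with cigarettes per day.**

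| Analysed per cell | Stratum OR | Power, both main effects | Family-wise type I error |
|---|---|---|---|
| 298 | 0.7 | 89.5% -> 89.6% | 5.0% -> 5.1% |
| 298 | 0.5 | 89.3% -> 89.6% | 4.7% -> 4.9% |
| 298 | 0.35 | 89.2% -> 89.9% | 4.3% -> 4.7% |
| 328 | 0.7 | 92.7% -> 92.7% | 4.7% -> 4.8% |
| 328 | 0.5 | 92.0% -> 92.2% | 5.0% -> 5.3% |
| 328 | 0.35 | 92.6% -> 93.2% | 4.0% -> 4.7% |

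The row of 328 is 298 x 1.10 = 327.8, the number analysed per cell after 20% loss from 410. The Monte Carlo standard error of a 5% rate is sqrt(0.05 x 0.95 / 6,000) = 0.3 points, so 5.3% is compatible with 5%.

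**4. Attenuation of the log odds ratio.** The conditional value is logit(0.175) - logit(0.105) = 0.592. Averaging over a 60% stratum with overall control abstinence held at 10.5%:

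- OR 0.7: marginal 0.590, attenuation 0.4%.
- OR 0.5: marginal 0.584, attenuation 1.4%.
- OR 0.35: marginal 0.573, attenuation 3.2%.

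With 40% to 75% in the 11+ stratum, the range is 0.3% to 3.2%.

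**5. Loss that depends on arm and stratum (illustration).** Assume no treatment effect and 60% smoking 11+. Follow-up is 85% in both strata of one arm; in the other it is 90% for lighter and 65% for heavier smokers. The share of heavier smokers among completers stays at 60% in the first arm. In the second it is 0.6 x 0.65 / (0.6 x 0.65 + 0.4 x 0.90) = 0.39 / 0.75 = 52%. With overall abstinence of 14%, the model without the stratum shows a spurious log odds ratio of 0.03 (OR 0.7), 0.06 (OR 0.5) or 0.08 (OR 0.35). If follow-up in the second arm is 88% and 78%, the values are 0.01, 0.02 and 0.03. Conditioning on the stratum removes this part.

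**6. Hospital as random or fixed.** With cigarettes per day in both models (600 trials per scenario), power agreed within 0.2 points and type I error was identical.

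**The case against.** The strongest objection is that silence is not exclusion. The text is a condensed article with no covariate list. It nowhere calls the model unadjusted, and a full protocol or analysis plan that is not shown may already contain the term. This stands as far as it goes: a reader might infer that the plan excludes cigarettes per day, and the document does not support that. What remains is that the article fixes the model family, the hospital effect, the software and the multiplicity rule, and gives a role to only one stratum. The request is for a specific term, and if it is already planned, one confirming line settles the matter.

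A second objection is that the harm is slight. This also stands. Type I error without the stratum is neutral to slightly conservative. The attenuation is non-collapsibility, the gap between a marginal and a conditional odds ratio, rather than bias in the randomised comparison.

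A third is that the prognostic strength is assumed. The Design section gives balance across conditions as the purpose of stratifying, and the link to the patch regimen could by itself explain the choice of factor. Hence the range of odds ratios above.

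**Conclusion.** The point holds as a minor one: cigarettes per day is a randomisation stratum without a stated place in the primary model, and including it is better than leaving it out. The expected gain is about 0 to 0.7 points of joint power, up to about 3% less attenuation of the conditional log odds ratio, type I error a little nearer 5% where the stratum is strongly prognostic, and some protection against loss that depends on arm and smoking level. These sizes rest on assumed stratum odds ratios of 0.7 to 0.35 and on the assumed prevalence, hospital spread and loss patterns. No stated sample-size figure changes.

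Three stronger readings are not supported:

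- *That the primary result is at risk.* Nothing above shows inflated error or a material loss of power.
- *That five hospitals are too few for a random effect, so hospital must be fixed.* The between-hospital variance is poorly estimated with five hospitals, but subjects are randomised within hospital, so the treatment effects hardly depend on it. Random and fixed gave practically the same tests.
- *That the 10% clustering allowance is an error because hospital intercepts cancel from the treatment contrasts.* That argument covers intercepts only. Recruitment and patch delivery differ between the two health-care systems, so treatment effects could vary by hospital, and such variation would not cancel. The allowance is conservative.

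**What to change.** State in the analysis plan that the primary binomial mixed model contains the two treatment factors, the hospital random effect, and the cigarettes-per-day stratum (6 to 10 versus 11 or more, as used at randomisation) as a fixed covariate. If the full plan already says so, a confirming sentence is enough.

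The cost is one sentence. Cigarettes per day is entered on the website at randomisation for every subject, so no new data are needed. Recruitment is described as ongoing, and the sentence should be in place before outcomes are compared by arm. The hospital random effect, the 10% allowance and the sample size can stay as they are.
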